##### Occupational therapy—activities of daily living

Participants with a FRS [76] ≤2, at baseline, in one or more of the following categories: grocery shopping, cooking, or eating (not including dysphagia) are offered an intervention by a community-based occupational therapist starting within two weeks after discharge.

The choice of intervention is based on the Assessment of Motor and Process Skills (AMPS) [78], which evaluates the quality of performed activities of daily living (ADL) according to the degree of physical effort, efficiency, safety, and independence. Following this assessment, an appropriate activity-based intervention is planned by the occupational therapist in collaboration with the participant according to the principles of the Occupational Therapy Intervention Process Model (OTIPM) [79]. If there is potential to maintain or regain functional ability, then the participant is offered 1-h home visits by a community-based occupational therapist during the first 16 weeks after discharge for up to 7 home visits or until the goal of intervention is reached. In collaboration with the participant, the therapist sets the goal of maintaining or regaining functional ability in groceries shopping, cooking, and/or eating. If there is no potential to maintain or regain functional ability, then the intervention is terminated after the first home visit.

##### Physiotherapy

Participants who screen positive for low functional ability (i.e., FRS scores ≤2 in grocery shopping, cooking, or eating) are also evaluated for lower extremity strength during baseline data collection. Decreased muscle strength is defines defined as <5 repetitions on 30 s sit-to stand test [80, 81] or 5–8 repetitions on 30 s sit-to stand test in combination with a 4-m gait speed [82] below 0.6 m/s [81]. Participants with decreased muscle strength at baseline are re-evaluated at 2–3 weeks after discharge by a community-based physiotherapist. Participants who still have decreased muscle strength at this timepoint are offered two weekly training sessions [83] by a community-based physiotherapist for 16 weeks after discharge. The training sessions are approximately 1-h in duration and take place either in the participants home or at a training facility. The training is intended to improve the participant’s ability to maintain independent ADL by combining exercises for strength, endurance, and balance [84]. The specific exercises include a progressive sit-to-stand exercise as reported by Pedersen et al. [85], a static balance exercise, where the participant pokes for the hands of the physiotherapist to train the participant’s agility [86] by altering the base of support for 3 sets of 10–60 s, an up-and-down-from-floor exercise, a stair climbing exercise till fatigue or for a maximum of 10 min and a walking exercise, aiming to increase step counts by 10% each week [87], based on the walking capabilities of the participant. Participants with unsafe walking abilities will have supervised walking for 10 min with the physiotherapist. All exercises follow prespecified algorithms for training progression and are adjusted accordingly for each session. During the intervention, participants are also weighed once each week by the physiotherapist. If a participant has > 1 kg weight loss since the first training session, then training is paused, and a dietician provides dietary counseling until body weight is stabilized, at which point training is resumed.

##### Evaluation of depression and treatment

Participants are screened during baseline data collection for depression using the Mini Geriatric Depression score [88]. Participants with a Mini Geriatric depression score ≥2 are subsequently screened with the Geriatric Depression Score-15 (GDS-15) [89]. Participants with a GDS-15 ≥5 are offered evaluation and treatment for depression by a geriatrician during hospitalization. After discharge, the geriatrician can follow up on treatment by phone. If the participant is discharged before evaluation and treatment by the geriatrician, then they are recommended to see their GP.

##### Oral health-related intervention

Participants are screened during baseline data collection for oropharyngeal dysfunction. Participants who report oral pain, masticatory difficulties, and/or xerostomia (Summated Geriatric Xerostomia Inventory≥8) [90] are offered a clinical oral evaluation including diagnosis of potential oral and/or dental disease conditions by a research dentist. This evaluation includes an interview on oral symptoms and an evaluation of the dental, periodontal and oral mucosal status, the oral hygiene status, and functional occlusion as well as the function of dentures (partial or full, if present). In case of suspicion of oral candidiasis, an oral smear is performed, and antifungal treatment initiated if necessary. Overall, if dental treatment is required, the participant is advised to attend to their dentist. If the oral hygiene is insufficient and the participant displays signs of gingivitis and periodontitis and/or impaired salivary gland function, they are offered two home visits from a dental hygienist after discharge. This intervention includes instruction and motivation in order to improve the oral hygiene and thereby oral health. Participants with insufficient oral hygiene are also provided with an electrical toothbrush.

#### Training of staff performing the interventions

All clinical pharmacists are educated and certified by The Capital Region Pharmacy, Herlev, Denmark, to perform medication reconciliation and medication reviews. All clinical pharmacists are provided 1 h of instruction about the intervention by CT, [name], or the primary investigator [name]. Additional instruction may be provided by [name] as needed during the trial.

Both hospital- and community-based dieticians are provided one hour of instruction about the intervention by the primary investigators, [name], or [name]. This instruction reviews standardized procedures for data collection and dietary interventions and may be repeated if deemed necessary. Hospital-based dieticians are also provided supervised training in dietary interventions by [name], [name], or already trained dieticians until deemed ready to perform the intervention unsupervised. Additional instruction may be provided by [name] or [name] as needed during the trial.

Both hospital- and community-based occupational therapists and physiotherapists are provided 1 h of instruction about the intervention by primary investigators [name] or [name]. This instruction reviews standardized procedures for data collection and therapy interventions and may be repeated on an individual basis upon request.

#### Compliance

Participant compliance is defined separately for each element of the intervention. Compliance to medication review is defined as having received a medication review that is evaluated and effectuated by a geriatrician. Compliance with dietary counseling is defined as having counseling during hospitalization and ≥3 home visits after discharge. Compliance with physiotherapy is defined as having received ≥75% of training sessions. Compliance with occupational therapy is defined as having received ≥75% of the home visits for dysphagia and ≥75% of home visits for ADL if deemed relevant by the occupational therapist. Compliance to evaluation and treatment of depression is defined as having received an evaluation by the geriatrician. Compliance with oral health-related intervention is defined as having received an evaluation by a dentist and ≥1 home visit by a dental hygienist if deemed relevant by the dentist.

#### Adherence

Recruitment, data collection, and interventions are all performed either in the hospital (during hospitalization) or in the participant’s home (after discharge). This strategy is performed to maximize patient recruitment, data collection, and compliance to the intervention while minimizing participant transportation costs and efforts. Adherence to the intervention is registered and evaluated but not monitored during the trial.

### Outcomes

Trial outcomes as well as timepoints and collection methods for each outcome are shown in Table 2 and Fig. 3.

**Table 2 Tab2:** An overview of all outcomes in the OptiNAM-trial

Variable	Instrument	Time point
Primary outcomes		
Health-related quality of life	EuroQol-5D-5L is a self-reported questionnaire comprised of 5 questions concerning: mobility, self-care, usual activities, pain/discomfort and anxiety/depression, and a visual analog scale (VAS-scale). Each question has 5 response categories, ranging from having no problems to being unable. The responses are converted into an index value, reflecting the health status compared to the reference of the general population (norm data) [91, 92]. The VAS-scale ranges health at a scale from 0 (worst health you can imagine) to 100 (best health you can imagine).	t_1_, t_2_, t_3_, t_1y_
Medication appropriateness	Medication Appropriateness Index-score (MAI-score) consists of 10 criteria addressing different aspects of each prescription, including indication, effectiveness, dose, direction, practical direction, drug–drug interaction, drug–disease interaction, duplication, duration of therapy, and cost [93]. Each criterion has operational definitions that instruct the evaluator to rate a medication as (A) appropriate, (B) marginally appropriate, (C) inappropriate, or (Z) do not know [94]. Each of the criteria is assigned a score between 0 and 3 according to a standardized protocol. Each prescription can obtain a score between 0 and 18 [95], where 0 represents appropriate prescribing and higher scores indicate a greater degree of inappropriateness.	t_1_, t_2_, t_3_
Kidney function	The glomerular filtration rate (GFR) is determined according to the single-injection plasma clearance method [96, 97]. Radioactivity is measured in multiple venous blood samples obtained between 180 and 300 min after a single intravenous injection of 40 MegaBecquerel ^99m^Technetium–diethylenetriaminepentaacetic acid (^99m^Tc-DTPA) and GFR is calculated from the plasma disappearance curve of ^99m^Tc-DTPA.	t_GFR_
Confirmative outcomes		
Underutilization of medication	The Assessment Of Underutilization (AOU) index identifies omitted medication prescribing despite being indicated [98]. The evaluation requires a full medication list as well as a list of established medical conditions to apply one of three ratings for each condition: (A) no omission, (B) marginal omission, or (C) omission of an indicated medication without contraindication [94].	t_1_, t_2_, t_3_
Pharmacogenetic	DNA material is collected by a buccal swab. The genetic test involves variations in 14 genes and copy variants responsible for drug transport and metabolism of more than 140 commonly prescribed medications. The included genes are Cytochrome P450 (CYP) 1A2, 2B6, 2C19, 2C8, 2C9, 2D6, 3A4, 3A5, Dihydro-pyrimidine Dehydrogenase, Opioid Receptor Mu 1, Solute Carrier Organic Anion Transporter Family Member 1B1 (SLCO1B1), UDP glucuronosyltransferase family 1 member A1, UDP-glucuronosyltransferase 2B15, and Vitamin K epOxide Reductase Complex subunit 1 [99]. After genomic data translation, a personalized evidence-based report is generated based on recommendations from the Food and Drug Administration drug labels, PharmGKB and Clinical Pharmacogenetics Implementation Consortium guidelines [100, 101]. The Pillcheck software (GeneYouln Inc., Toronto/Ontario, Canada) is used for the categorization of metabolic status classes linked to evidence-based recommendations for drug prescribing, and for identifying medications that may cause reduced clinical efficacy or significant drug reactions at standard starting doses [26].	t_1_
Dietary intake	Macronutrient intake is assessed based on validated dietary records or 24-h recalls and calculated with the software VITAKOST (VITAKOST ApS, Kolding, Denmark) [74]. During hospitalization, daily dietary records are kept by the participant and validated by a dietician (only two days for participants in the control group). At follow-up visits in weeks 8 and 16, a 3-day dietary record is validated by a dietician using household measures and photo material [102] to estimate portion sizes. In case of missing dietary records, a 24-recall [73] is performed instead, which also is validated by a dietician using household measures and photo material [102].	During hospitalization , t_2_, t_3_
Mobility	Maximal hand grip strength is measured with a hand dynamometer (Saehan, Digi-II) in three attempts [103]. If the last attempt is the peak value, another two attempts are given as described by Bodilsen et al. [104]. A 30-s chair-stand-test measures the number of full rises from a sitting position in a chair without support from the arms performed in 30 s [80]. A 4-m walking test measures habitual walking pace (m/s) on a 4-m long track [105]. The De Mortons Mobility Index (DEMMI) measures the ability to perform mobility tasks of increasing difficulty, from transferring in bed to jumping. DEMMI provides a crude score from 0 to 19, which is converted to a DEMMI-scale score from 0 to 100, where 100 is the highest level of mobility [106–109]. ActivPAL® is an accelerometer (PAL Technologies Ltd., Glasgow, UK) [110], mounted mid-thigh which measures time spend lying/sitting, standing, and walking and daily number of steps.	t_1_, t_2_, t_3_ 1^th^ week after discharge, t_2_, t_3_
Activity of daily living	The Functional Recovery Score measures the degree of dependency in 11 different ADL [76].	t_1_, t_2_, t_3_
Well-being	The 5-item World Health Organization Well-Being Index measures well-being on a scale from 0 to 100, where 100 is the highest level of well-being [111].	t_1_, t_2_, t_3_
Frailty	Fried’s frailty phenotype evaluates frailty on 5 aspects: measured Hand Grip Strenght and walking pace, self-reported physical activity level, exhaustion, and weight loss [112]. The FRAIL questionnaire [113] includes questions concerning fatigue, capability of stair climbing, walking distance, multi morbidity, and weight loss. The Frailty Index, FI-Outref [114], is calculated by using the number of admission laboratory test results being outside the reference interval.	t_1_, t_2_, t_3_
Anthropometry	Body weight is measured with or without shoes and in light clothing. Waist circumference is measured in a standing position after a normal exhalation. Self-reported height is registered.	t_1_, t_2_, t_3_
Body composition	Total and segmented lean body mass and bone mineral content are measured with whole-body Dual-energy X-ray Absorptiometry (DXA) (GE Lunar Prodigy Primo, GE Healthcare Technologies, Madison, Wisconsin, US). DXA-scan is a clinical standard and validated to assess body composition [115]. Total and segmented body fat, fat-free mass, soft lean mass, bone mineral content, and intra- and extracellular water are measured using Bioelectrical Impedance Analysis (BIA) performed with InBody S10 [116]. Standardization, regarding fasting, physical activity, and urination prior to the measurement are not possible due to the acute setting. Information on these parameters is therefore collected prior to the measurement.	t_GFR_ During admission, t_1_, t_2_, t_3_ and t_GFR_
Blood pressure and heart rate	In a sitting, relaxed position blood pressure and heart rate are measured with a Microlife, BP A3L Comfort, automatic monitor, 3 times in a row on the right upper arm, with a break of 30 s in between measurements.	t_1_, t_2_, t_3_
Mortality	The Danish Register of causes of death [117] is a national registry where the cause of death noted in the medical evaluation after death is gathered.	t_1_, t_2_, t_3,_ t_1y_
Cognition	The trail making test [118] assesses the time it takes the participant to draw a line between 25 consecutive numbers that are scattered randomly on a piece of paper and are recorded. In the Digit Symbol Modalities test [119], the participant fills in as many as possible digits corresponding to a symbol in 90 s. The number of correctly filled in digits is recorded. In Hopkins Verbal Learning Test Revised [120], 12 words are read out loud, and the number of recalled words are recorded. Further, a list containing the 12 words and other words is read out loud, and the correctly and incorrectly recognized words are recorded. A delayed recall is of the 12 words is furthermore performed. The Mini-Mental State Examination [121] consists of 11 questions and tasks and provides a score between 0 and 30. The Orientation-Memory-Concentration test [122] consists of three questions concerning time and place, two tasks of concentration, and one task on memory.	t_2_, t_3_ t_2_, t_3_ t_2_, t_3_ t_2_, t_3_ t_1_, t_2_, t_3_
Depression	The Mini-Geriatric Depression Score [88] measures the need for medical evaluation of depression with 5 yes/no questions.	t_1_, t_2_, t_3_
Nutritional risk status	The Mini Nutritional Assessment- short form [60] is a screening tool, consisting of 6 questions concerning food intake, weight development, mobility, acute illness, cognition, and BMI. The result classifies the patient as malnourished, at risk of malnutrition or having normal nutritional status. The Nutritional Risk Screening-2002 [123] classifies the patient’s risk of malnutrition based upon a primary and a secondary screening. The primary screening consists of 4 yes/no questions. If one answer is yes, the secondary screening is performed. The secondary screening evaluates the degree of illness and malnutrition. The Eating Validation Scheme [124] is a screening tool that classifies a person as having no risk of malnutrition, at risk of malnutrition or in need of nutritional intervention based on evaluation of eating habits, weight development, and risk factors of malnutrition. The Eating Symptom Questionnaire [125] clarifies if 13 different difficulties (e.g. nausea, dry mouth, pain) are related to the development of malnutrition. The Simplified Nutritional Appetite Questionnaire [126] identifies persons with anorexia and risk of weight loss by asking 4 questions on appetite, fullness, taste, and number of daily meals. The Global Leadership Initiative on Malnutrition (GLIM) criteria [127] is a consensus-based 2-step approach for malnutrition diagnosis. The first step is screening for malnutrition and the second step is the assessment of malnutrition diagnosis and grading of malnutrition severity. Malnutrition is diagnosed if at least one phenotypic criterion (non-volitional weight loss, low body mass index, and reduced muscle mass) and one etiologic criterion (reduced food intake or assimilation and inflammation or disease burden) are present. The European Society of Clinical Nutrition and Metabolism statement [128] is a European consensus-based set of criteria for the diagnosis of malnutrition. After a positive screening result for malnutrition, malnutrition is diagnosed based on low body mass index or on unintentional weight loss together with low BMI or low fat-free mass index	t_1_, t_2_, t_3_
Dysphagia	The Eating Assessment Tool-10 (EAT-10) [71, 72] is a 10-question questionnaire which identifies persons with a need for evaluation of dysphagia.	t_1_, t_2_, t_3_
Intestinal microbiome	All participants at risk of malnutrition or with malnutrition according to the nutritional screening tool MNA-SF will collect a fecal sample using EasySampler [129]. Samples collected during hospitalization are frozen as fast as possible at −80°. If collected in the home of the participant, the sample is frozen as fast as possible in the participants own −18° freezer for maximally 3 days. The samples are transferred in a cooler bag with freezer elements to the −80° freezer (Biobank). At the time of collection, the participant reports where the sample belongs on the Bristol Stool Scale [130] and their use of antibiotics.	t_1_, t_2_, t_3_
Blood samples	Blood samples are analyzed for: Alanine aminotransferase, albumin, basic phosphatase, bilirubin, carbon dioxide, C-reactive protein, hemoglobin, coagulation factors II, VII, and X International Normalized Ratio, potassium, urea, coagulation factors, leukocytes, neutrophils, mean corpuscular hemoglobin concentration, mean cell volume, sodium, platelets, lactate dehydrogenase, neutrophil gelatinase-associated lipocalin, BTP and B2M, soluble urokinase plasminogen activator receptor, cholesterols, triglycerides, blood sugar, glycated hemoglobin, insulin, markers of the effect, and plasma levels of medication. Calculation of eGFR will be based on the Chronic Kidney Disease Epidemiology Collaboration [131–133], Berlin Initiative Study [132], Full Age Spectrum [42, 134, 135], Lund-Malmö revised [136], the Caucasian and Asian pediatric and adult subjects [137], Modification of Diet in Renal Disease [138], and Cockcroft-Gault [42] equations based on creatinine, cystatin C, B2M or BTP, or a combination of the markers.	t_1_, t_2_, t_3_, t_GFR_
Health economics	Use of health care services will be collected from the following registries: National Patient Registry, National Health Insurance Registry, The Danish National Prescription Registry [139], and local databases in the municipalities.	t_1-_ t_3_ and t_1_-t_1y_
Descriptive variables	Participant characteristics are based on participant self-report or obtained from the medical journal and include sex, age, civil status, living conditions, education, smoking status, alcohol consumption, physical activity level, use of home- and health care, early warning score and diagnoses.	t_1_

Timepoint for: baseline: t1, follow-up 8 weeks after discharge: t2, follow-up 16 weeks after discharge: t3, follow-up by telephone 1 year after discharge: t1y, assessment of glomerular filtration rate (GFR): tGFR

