### Aims

The study involving acutely admitted older medical patients has three primary aims (1) to determine whether a medication review intervention is superior to standard care in improving medication appropriateness from admission to 8 weeks after discharge, (2) to determine the accuracy of eGFR equations based on various biomarkers compared to mGFR at a single-time point, and (3) to determine whether an individualized multimodal and transitional nutritional intervention is superior to standard care in improving the quality of life from admission and 16 weeks after discharge.

The study also has the following secondary aims which are related to the effect of the intervention: (1) to measure differences in polypharmacy, PIM use, and assessment of underutilization between the MED-intervention and standard care from admission to 8 weeks after discharge and (2) to measure of the differences in body weight, protein- and energy intake, mobility, cognition, frailty, the intestinal microbiome, and health care costs between the MULTI-NUT-MED intervention and standard care from admission to 8 and 16 weeks after discharge and 1 year after discharge (only health care costs).

Secondary aims, which are based on baseline data or data from the control group, include assessment of (1) how information from a broad pharmacogenetic test can potentially improve medication prescribing appropriateness; (2) how polypharmacy, PIMs, nutritional status, frailty, and inflammation modify the effect of the MED-intervention on prescribing appropriateness; (3) how non-GFR determinants affects eGFR and how the choice of eGFR equation affects medication prescribing; (4) how the choice of malnutrition classification criteria affects the prevalence of malnutrition; and (5) how different definitions of frailty affect the distribution of patients classified as frail or sub-frail as well as the responsiveness of these methods.

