#### Dietary counseling

Dietary counseling is provided both during hospitalization, by research dieticians, and after hospital discharge by community-based dieticians or by hospital-based research dieticians if community-based dieticians are not available. The goal of dietary counseling is to ensure that each participant receives a diet that covers the energy and protein requirements to either maintain their body weight (if BMI≥18.5) or gain body weight (if BMI <18.5). Both the content of the dietary counseling and the structure of the home visits after discharge are inspired by Lindegaard et al. [68, 69].

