### Sample size

The trial has three primary endpoints that build on mutually independent hypotheses [140]. Therefore, sample size calculations were performed for each endpoint as described below. All sample size calculations are performed for a significance level of 5%, power of 80%, and a dropout rate of 25%. Ethical approval was obtained for the inclusion of 200 participants in total to ensure enough power for all primary endpoints.
1: Based on a *t* test, a sample size of 120 is required to detect a clinical difference of 3 points (SD=5 points [36]) in MAI score change from baseline to 8 weeks after discharge between the control group and pooled intervention group (MED and MULTI-NUT-MED intervention).2: Based on a paired *t* test, a sample size of 62 participants is required to detect a clinically relevant difference of 4.0 mL/min/1.73m^2^ (SD=15, a R=0.73 [141]) between mGFR and eGFR based on the combination of creatinine and cystatin C. GFR is measured at baseline for all trial participants regardless of group allocation.3: Based on a *t* test, a sample size of 130 participants with or at risk of malnutrition is required to detect a clinically relevant difference of 0.15 points [142] (SD=0.27 [143]) in EuroQol-5D-5L score change from baseline to 16 weeks after discharge between the control group and MULTI-NUT-MED intervention group, assuming equal allocation in the two groups.

Given that patients are included independently of nutrition status and approximately 70% of patients are expected to have or be at risk of malnutrition [4], a total of 185 participants is required to achieve a sample size of 130 participants with or at risk of malnutrition.

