### Blinding

The nature of the intervention does not allow blinding of participants or personnel performing the intervention. However, the outcome assessor is blinded to the result of the randomization throughout the trial, and all data analysis is performed blinded.

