## Methods: data collection, management, and analysis

### Data collection methods

Depending on the outcome, data collection is performed at baseline (t_1_), 8 weeks after discharge (t_2_), 16 weeks after discharge (t_3_), 1 year after discharge (t_1y_), and at the GFR-measurement (t_GFR_) (Tables 1 and 2).

Data collection is performed by the same assessor whenever possible to minimize variation. All assessors are provided supervised training in data collection by primary investigator [name], [name], [name], [name], or [name] until deemed ready to perform data collection unsupervised. Data are collected in the ED at baseline and in each participants’ home during follow-up. If a participant declines full data collection at follow-up, then they are offered minimal data collection consisting of blood samples, body weight, MNA-SF, EuroQol-5D-5L, blood pressure, heart rate, hand grip strength, and body composition with BIA. If the participant declines minimal data collection, then they are offered to complete any components of data collection that can be performed by telephone interview. A full medication list for each participant is recorded at every follow-up visit, and the patient’s diagnosis codes and laboratory tests are accessed in the patient chart and stored for future MAI and AOU scores assessment. A full medication list for each participant is recorded at every follow-up visit, and the patient’s diagnosis codes and laboratory tests are accessed in the patient chart and stored for future calculation of MAI and AOU scores. A self-reported medication list is obtained by a senior pharmacist through interviewing the participant, and this list is cross-referenced with the Shared Medication Card. If there are any discrepancies between medications reported by the patient and those found in the Shared Medication Card, then the senior pharmacist confirms the medications by contacting the participant’s relatives, home care personnel, or GP. Registry data (see Table 2) are obtained retrospectively.

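### Table 2 lets body weight, a secondary outcome, be taken with or without shoes and states no rule to keep, record or correct for footwear; this adds avoidable error, probably small between arms

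*Protocol article*

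**What the plan says.** The Anthropometry row of Table 2 (Protocol article, Outcomes) gives the whole weighing rule: "Body weight is measured with or without shoes and in light clothing". It applies at baseline, week 8 and week 16.

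Body weight is an endpoint of the nutritional comparison. The secondary aims include "to measure of the differences in body weight, protein- and energy intake, mobility, cognition, frailty" between the MULTI-NUT-MED intervention and standard care, and Table 1 lists anthropometry among the confirmative outcomes.

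The setting changes between visits: "Data are collected in the ED at baseline and in each participants’ home during follow-up" (Data collection methods). On blinding, "the outcome assessor is blinded to the result of the randomization throughout the trial"; participants and intervention staff are not blinded (Blinding).

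The next row of Table 2, on body composition, handles a similar difficulty differently. Fasting, activity and urination before bioimpedance cannot be standardized in the acute setting, so the plan collects information on them. The weight row has no such step.

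**The concern.** The rule expressly permits either state at each weighing and does not tie follow-up to baseline. If a participant is weighed barefoot in the ED and shod at home, or the reverse, the recorded change is the true change plus or minus the weight of the shoes. The move from hospital to home makes such a switch plausible.

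The counseling aims "to either maintain their body weight (if BMI≥18.5) or gain body weight (if BMI <18.5", so for many participants the intended change is none or small, and a fixed error counts for more against it.

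Three uses of weight could be affected: change in an individual, mean change within an arm, and the between-arm difference in change, which is the endpoint. BMI is also a component of MNA-SF, GLIM and ESPEN (Table 2, Nutritional risk status). For BMI no switch is needed: any weighing with shoes raises it.

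**Working it through.** **Inputs from the documents.** The plan has no effect size, SD or power for body weight, so there is no weight figure to reproduce. The sample comes from the quality-of-life calculation: "a sample size of 130 participants with or at risk of malnutrition is required to detect a clinically relevant difference of 0.15 points". A two-sample t test with difference 0.15, SD 0.27, two-sided 5% and 80% power gives 52 per arm, 104 in total, and 104 × 1.25 = 130. With the stated 25% dropout, 130 × 0.75 = 97.5 remain, or 48.75 per arm.

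**Assumptions, not in the documents.** Shoe weight s is 0.5 to 1 kg (0.3 and 1.5 kg as outer values). SD of true weight change is 2 to 5 kg. The test is two-sided at 5%, and the planned multiplicity adjustment for confirmative outcomes is ignored.

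**Step 1: one participant.** The error in change is 0 if the state is the same at both visits, and +s or −s if it differs.

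**Step 2: mean change within an arm.** If the share wearing shoes moves from p1 to p2, the mean shifts by (p2 − p1) × s. For a move from 20% to 80% this is 0.6 × 0.5 = 0.30 kg or 0.6 × 1.0 = 0.60 kg.

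**Step 3: between-arm difference.** If footwear is unrelated to arm, the shift in Step 2 is the same in both arms and cancels. What remains is variance. With independent wearing, the added variance of change is [p1(1 − p1) + p2(1 − p2)] × s². At 50% for both visits this is 0.5 s², the largest value under independence. The 20%-to-80% pattern gives 0.32 s². At 50% the added SD is √(0.5 × 0.25) = 0.35 kg for 0.5 kg shoes and √0.5 = 0.71 kg for 1 kg shoes.

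The difference detectable with 80% power and no footwear error is (1.96 + 0.8416) × SD × √(2/48.75). This gives 1.13, 1.70, 2.27 and 2.84 kg for SDs of 2, 3, 4 and 5 kg. Power for those same differences after replacing SD by √(SD² + 0.5 s²):

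| SD of change | s = 0.3 kg | 0.5 kg | 1.0 kg | 1.5 kg |
|---|---|---|---|---|
| 2 kg | 79.6% | 78.8% | 75.2% | 69.7% |
| 3 kg | 79.8% | 79.5% | 77.8% | 75.2% |
| 4 kg | 79.9% | 79.7% | 78.8% | 77.3% |
| 5 kg | 79.9% | 79.8% | 79.2% | 78.2% |

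At SD 3 kg the detectable difference rises from 1.70 kg to 1.71 kg (0.5 kg shoes) or 1.75 kg (1 kg shoes).

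**Step 4: bias between arms.** This needs footwear habits that differ by arm. A 20-point difference at follow-up with 1 kg shoes gives 0.2 × 1.0 = 0.20 kg. Nothing in the documents shows such a difference.

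**Step 5: BMI.** Height is a constant divisor, so BMI moves by the same percentage as weight. For an assumed 60 kg person this is 0.5/60 = 0.8% to 1.0/60 = 1.7%. At a BMI of 18.5 that is 0.15 to 0.31 kg/m², enough to matter only close to a cut-off.

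**After the fix.** With a constant footwear state, or shoe weight subtracted, the added variance and the shift in change are both 0. Removing shoes or subtracting their weight also clears the BMI error.

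**The case against.** The strongest reply is that the endpoint is a randomized contrast with a blinded assessor. A footwear change common to both arms cancels, and the remaining noise is small unless shoes are heavy or the SD of change is low. This stands, and it limits the point to a minor one. It does not cover within-arm change, individual classification, or habits that might differ by arm among unblinded participants.

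A second reply is that the article condenses a fuller procedure. Assessors receive supervised training, and the same assessor is used whenever possible, so footwear may in practice be kept constant or recorded. It is therefore not shown that footwear went unrecorded. But the published rule does more than leave detail out: it allows both states.

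Three stronger readings are tempting, and the documents do not support them.

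- A reader might infer that weight change necessarily includes footwear, in an amount important for this endpoint. It does so only when the state differs between visits, and the documents give no important difference or SD for weight against which to judge the amount.
- A reader might take the physiotherapy rule, "If a participant has > 1 kg weight loss since the first training session, then training is paused", as the protocol's threshold for an important weight change. It governs separate weekly weighings by the physiotherapist, counted from the first training session, and says nothing about the outcome at weeks 8 and 16.
- A reader might extend the error to the FRAIL and Fried weight-loss items. Table 2 describes FRAIL as a questionnaire and appears to list Fried's weight loss with the self-reported items. Nothing shows that either uses scale weight. For GLIM and ESPEN, the documents do not say that weight loss is computed from trial weighings, so only the BMI component is argued here, and even there the source of the weight is not spelled out.

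**Conclusion.** The point holds as a minor measurement flaw. The weighing rule permits a mixed footwear state for a secondary outcome, with no stated safeguard and a change of setting between visits. Individual and within-arm weight change may carry footwear error, as may BMI in MNA-SF, GLIM and ESPEN.

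For the between-arm comparison the cost is probably small: 0.5 to 2.2 power points for shoes of 0.5 to 1 kg at an SD of change of 3 kg, and about 5 points for 1 kg shoes at an SD of 2 kg. Within an arm, the mean could shift by 0.30 to 0.60 kg if shoe wearing moved from 20% to 80%. Shoe weight, wearing probabilities and SD are all assumptions. The 50% independent-wearing case is the least favorable under independence, and a stable habit would cost less. The primary outcomes do not use body weight and are not touched.

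**What to change.** Change the Table 2 rule to weigh without shoes at every visit. Where shoes cannot be removed, which may happen with acutely ill patients in the ED, record this and subtract the weight of the shoes. The cost is a few seconds per weighing and one recorded item.

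For participants already weighed, keep the baseline footwear state at later visits if it was recorded. Otherwise, report the limitation with the weight results. This second route may be the main one. The trial began in October 2018 with 100 weeks of recruitment expected, which runs to about September 2020, while the article is dated September 2021. On that schedule most or all weighings through week 16 were already past.
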